### Assignment of interventions

#### Allocation

##### Sequence generation

Participants will be randomly allocated to one of the groups before the surgical procedure after meeting the eligibility criteria with a ratio of 1:1. Randomization will be accomplished using random block sizes without stratification (block randomization) using statistical software approved for this purpose, e.g., from the website www.randomization.com. The goal is to obtain homogeneity between the groups.

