## Methods/design

The RARPEX trial is designed as a randomized, placebo controlled, surgeon- and patient-blinded superiority single-center study with two parallel groups. Randomization will be performed as a block randomization with 1:1 allocation.

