### Safety aspects

Robotic-assisted radical prostatectomy is a highly technically demanding procedure. High-volume surgeons with great experience have better results than low-volume surgeons with less experience [32].

To avoid bias based on the learning curve of the surgeons, every surgical procedure will be performed by a senior surgeon who has experience with at least 100 robotic-assisted radical prostatectomies. Administration of tranexamic acid at the beginning of the procedure by an anesthesiologist is a simple common procedure, performed on a routine basis, and no special training is necessary, and no complications are expected.

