### Data collection

A daily visit of the study patients will be made by clinical investigators or a delegated physician. All protocol-required information collected during the trial will be entered into the patient’s record form.

Patient identification on the case report form (CRF) is through their unique trial identifier, allocated at the time of recruitment. Data coding will be carried out at various stages during the study. The patient’s record form is subject to audit by the principal investigator (PI) and Institutional Review Board (IRB).

Preoperative data gathered include patient age, body mass index, American Society of Anesthesiologists physical status classification system score, and comorbidities. Intraoperative data to be collected include surgery duration (skin to skin), console time (console surgeon activity time), and weight of the prostate.

Laboratory tests will include blood cell count (BCC), hematocrit test, and plasmatic creatinine level at the beginning of the procedure, 3–6 h after the procedure, on POD 1, POD 2, and POD 7 in the morning.

The differences between the hematocrit and hemoglobin levels (eventually weighted for the grams of the prostatic tissue) and hemoglobin/creatinine ratios will be obtained.

The volume of the fluids in the drain will be measured on postoperative day 1, and if the volume does not exceed 200 ml for 24 h, the drain is extracted. If the volume will be higher than 200 ml/24 h and the creatinine level in the drain fluid exceeds 500 μmol/l, urinary leakage will be confirmed (29). Patients with confirmed urinary leakage or urinoma will be excluded from the evaluation.

Postoperative course assessments will include duration of intermediate/intensive care, hospital stay including readmissions for postoperative complications, reinterventions (reoperations, endoscopic and interventional radiology procedures), the reasons for readmissions, and transfusion rates. The patients will be seen by a clinical investigator 3 months after the surgery in an outpatient fashion. The evidence of complication and level of prostatic specific antigen (PSA) will be monitored. Upon completion of 200 patients, the statistical processing will be performed, and results will be unblinded.

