### Minimizing treatment bias

Administration of tranexamic acid at the beginning of the procedure by an anesthesiologist is a simple common procedure, performed on a routine basis, which eliminates a learning curve.

All patients will undergo robotic-assisted radical prostatectomy without pelvic lymphadenectomy using the same technique. All surgeons participating in the study are familiar with this procedure. The dorsal vein complex (DVC) will be sutured at the beginning of the procedure.

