A sufficient number of blood counts will be analyzed in order to acquire sufficient data. Meunier et al. described a decrease in hemoglobin level after a single major blood loss (due to the blood donation) even after 6 days [40]. Prospective data are also needed to answer questions about the timing and frequency of sampling after RARP [36].

Chan et al. proved that the results can be significantly affected by the weight of the prostate. A larger prostate could mean longer operating time and greater blood loss. Therefore, the results will be weighted for the grams of the prostatic tissue [41].

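### Several surgeons operate, but neither the allocation nor the unadjusted primary t test uses the surgeon: some precision is lost, without bias

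*Protocol article*

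**What the plan says.** - **Allocation.** Methods/design: "Randomization will be performed as a block randomization with 1:1 allocation". Sequence generation adds: "Randomization will be accomplished using random block sizes without stratification (block randomization", followed by the aim: "The goal is to obtain homogeneity between the groups".
- **Surgeons.** Minimizing treatment bias shows that there is more than one: "All surgeons participating in the study are familiar with this procedure". Their number and caseloads are not given. Safety aspects states: "High-volume surgeons with great experience have better results than low-volume surgeons with less experience". It limits operators to senior surgeons with at least 100 such operations, with this purpose: "To avoid bias based on the learning curve of the surgeons, every surgical procedure will be performed by a senior surgeon".
- **Data.** Data collection: "Intraoperative data to be collected include surgery duration (skin to skin), console time (console surgeon activity time), and weight of the prostate". The surgeon is not named in that list.
- **Analysis.** Statistical methods compares the hemoglobin drop by a two-sample t test allowing unequal variances. No covariate is named for it. The Discussion plans to weight results for prostate weight, and the health economic analysis plans covariate-adjusted regression. Neither mentions the surgeon.

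**The concern.** The primary outcome measures surgical blood loss, and the protocol itself treats the operator as relevant to results. Blocks without strata balance the total number per arm, not each surgeon's patients. One arm can therefore receive more of one surgeon's cases by chance. An unadjusted t test leaves any such difference in the estimate and counts all between-surgeon variation as residual noise.

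The experience threshold does not remove this. It screens out early learning, but it does not make surgeons above 100 cases alike.

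At stake are the width of the confidence interval, some power, and the reader's ability to see whether the arms were comparable by operator.

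**Working it through.** **1. The plan's own figure.** Sample size calculation gives 64 per group at α = 1% and β = 10%, without an SD. Solving backwards, two-sided:

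SD = δ / [(z₀.₉₉₅ + z₀.₉₀) × √(2/64)] = δ / (3.857 × 0.1768)

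This gives 14.67 g/l for δ = 10 (Primary and secondary endpoints), 11.73 for δ = 8 (the pilot difference in the Discussion) and 7.33 for δ = 5 (Sample size calculation). The stated size cannot be confirmed without an SD, so 14.67 with δ = 10 is used below as a working value.

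**2. Size of a chance imbalance, two surgeons with equal caseload (assumed).** The between-arm difference in one surgeon's share has SD √(0.25 × 2/n) for n per arm. The shift in the treatment difference is that imbalance times the gap between surgeon means. The gap is assumed to be 5 to 10 g/l.

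| n per arm | SD of imbalance | 95% range (×1.96) | Shift, gap 5 | Shift, gap 10 |
|---|---|---|---|---|
| 100 | 0.0707 | ±13.9 points | ±0.69 g/l | ±1.39 g/l |
| 64 | 0.0884 | ±17.3 points | ±0.87 g/l | ±1.73 g/l |

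The median absolute shift is smaller: 0.6745 × 0.0707 × (5 to 10) = 0.24 to 0.48 g/l at 100 per arm.

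**3. Simulation with two to four surgeons.** Assumptions: random blocks of 2, 4 or 6, equal caseloads, surgeon means evenly spread over 0, 5 or 10 g/l, within-surgeon SD 14 g/l, unequal-variance t test at 0.05, 3000 runs per setting.

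| Total N | Surgeons | Trials with a share difference over 10 points | 95% limit of absolute shift, range 5 | Same, range 10 |
|---|---|---|---|---|
| 128 | 2 | 24–25% | 0.86 g/l | 1.72 g/l |
| 128 | 3 | 43–45% | 0.70 | 1.41 |
| 128 | 4 | 50–51% | 0.65 | 1.30 |
| 200 | 2 | 16–17% | 0.70 | 1.40 |
| 200 | 3 | 26–29% | 0.57 | 1.15 |
| 200 | 4 | 27–30% | 0.52 | 1.01 |

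The mean shift is 0.0 g/l in every setting (at most 0.01 in absolute value). Type I error lies between 4.2% and 5.5%, which is nominal within simulation error (√(0.05 × 0.95/3000) = 0.4 points).

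**4. What adjustment gains.** Take total SD 14.67, δ = 10, α = 0.01 two-sided and 64 per group, so that unadjusted power is 90.0%. Adjustment removes the between-surgeon variance v, leaving SD √(14.67² − v).

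| Surgeons | Range | v / 14.67² | Adjusted power |
|---|---|---|---|
| 2 | 5 g/l | 2.9% | 91.0% |
| 3 | 5 | 1.9% | 90.6% |
| 4 | 5 | 1.6% | 90.5% |
| 2 | 10 | 11.6% | 93.7% |
| 3 | 10 | 7.7% | 92.5% |
| 4 | 10 | 6.5% | 92.1% |

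If 5 g is the intended target, the implied SD halves to 7.33, and a 5 g/l range then takes the shares shown here for 10 g/l.

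**The case against.** The strongest reply is that unstratified blocks are a valid choice in a single-centre trial of 200. Under concealed 1:1 allocation the estimate is unbiased, and the t test's standard error already contains the between-surgeon variation. That is correct, and the simulation bears it out.

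The protocol also narrows operator differences in more ways than the threshold. It fixes one surgical technique on one robotic system, omits lymphadenectomy, excludes non-standard procedures and blinds the surgeons. The 10 g/l gap exceeds the whole 8 g/l pilot treatment difference, so it is an upper case rather than an expectation.

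Three stronger readings are tempting and not supported:

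- **That the surgeon is the main driver of blood loss.** The article does not say so. The factor that it ties to blood loss is prostate weight: "A larger prostate could mean longer operating time and greater blood loss".
- **That the plan contradicts itself.** Homogeneity is worded as a goal, and Safety aspects claims only to avoid learning-curve bias, which restriction to experienced surgeons does address.
- **That the surgeon goes unrecorded.** The list of intraoperative data is not presented as exhaustive, and eligibility depends on the surgeon's experience, so the operator has to be identified for each case.

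It may also be said that covariates belong in an analysis plan that is not shown. That would answer a complaint about silence. Here the article names an unadjusted test, and a better one is available at almost no cost.

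**Conclusion.** The point holds as a modest matter of precision and transparency, and it is a cheap improvement. Neither allocation nor the named primary test uses an operator factor that the protocol itself regards as affecting results.

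With two to four equal-caseload surgeons and an assumed 5 to 10 g/l spread, the 95% range of the chance shift is about ±0.5 to ±1.7 g/l. That is about 6 to 22% of the 8 g/l pilot difference (0.52/8 to 1.72/8) at the edge of the range, and typically much less. Power would move from 90.0% to about 90.5 to 93.7%.

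The number of surgeons, their caseloads, the spread and the SD are all assumptions, and the power figures further assume the 10 g/l target and α = 1% two-sided. The validity of the randomisation and of the planned test is not in question.

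**What to change.** Before unblinding:

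1. Take the operating surgeon for every randomised patient from the operative record.
2. Replace the unadjusted t test as primary analysis with a prespecified linear model of the POD 1 hemoglobin drop on treatment and surgeon. Pool surgeons below a caseload that is fixed without sight of the allocation. Use heteroscedasticity-robust standard errors, which keep the unequal-variance property of the planned test. The t test can remain as a supporting analysis.
3. Report each surgeon's caseload by arm, under a code.

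The cost is one data item, one model term and a few degrees of freedom. The randomisation need not change: Trial status expected the last patient by February 1, 2022, so separate lists per surgeon would probably come too late, and they are not needed for validity. The learning-curve statement in Safety aspects can stand. If the code has already been broken, present the surgeon-adjusted model as a declared sensitivity analysis instead.

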##### Concealment mechanism

Opaque, sealed envelopes will be produced, labeled with the randomization number and containing a sheet that states the group allocation for the patient. Randomization envelopes will be used in consecutive order. Basic characteristics of the patient and the day of randomization will be documented on a data sheet so that compliance with the randomization scheme may be checked retrospectively. To maintain the double-blinding, the placebo and active ingredient are identical and cannot be distinguished by the appearance of the participants or staff. The code assigned to subjects will be kept sealed and will not be released until the end of the clinical trial. Cases in which the blinding must be unsealed, such as a serious adverse drug reaction, will be managed using a separate envelope created for each subject so that only their randomization is revealed. Randomization and blinding will not be revealed to the researchers until the end of the study. If patients are excluded from the study after randomization, their numbers will not be reused.

##### Implementation

Unblinded nurse will prepare an infusion set according to the information in the sealed envelope with the patient’s study number on the day of the procedure. For patients in the intervention group 1, the dose of tranexamic acid according to target 20 mg/kg will be added to 100 ml of physiological saline. For patients in the intervention group 2, she will add no other substance to 100 ml of physiological saline. Infusion will be given into the sealed envelope, sent to the operating theater, and given within 5 min after the robotic system is docked.

#### Blinding

The double-blind randomized experimental scheme of the study allows to limit the statistical bias as well as the intervention bias. So, active treatment (tranexamic acid) and placebo will be allocated in blind: neither the patient nor the operating surgeons, attending physicians, nursing staff, and outcome assessors will know the allocated treatment. Furthermore, the presentation and the packaging of active treatments and placebos will be identical.

#### Unblinding

The unblinding will be carried out systematically at the end of the study. The study team members and healthcare providers do not have access to the treatment allocation code. However, if an investigator wants to introduce a medication that should be not taken at the same time to the study treatment, the blinding code will be broken. No expected adverse event in the study will require an emergency unblinding. In case of suspected unexpected serious adverse reaction, the sponsor will declare the serious and unexpected adverse reaction to the health.

### Study treatment

Based on the literature [16–18], and our pilot study [29], we decided to administer a single dose of tranexamic acid, corresponding to 20 mg/kg in 100 ml saline to all patients in the treatment group 1 at the beginning of the procedure. In the control group 2, we administer only 100 ml saline as placebo.

For prophylaxis of venous thromboembolism (according to the rules of our institution), the combination of mechanical device (graduated compression stockings) and pharmacologic agents (low-molecular weight heparin (LMWH)) in both treatment groups will be used. The prophylactic dose of LMWH is administered in the evening before the procedure, and the next dose at least 8 h after the procedure and then every evening at least till POD 7. Antibiotic prophylaxis is provided by a single dose of potent aminopenicillin as recommended by the antibiotic center: fluoroquinolone in patients with an allergy to aminopenicillin. During the procedure, the console time and weight of the prostate are monitored. Relevant concomitant care and interventions are permitted if necessary.

The surgical technique is standardized and has been described previously [30]. Standard robotic-assisted radical prostatectomy without pelvic lymphadenectomy using DaVinci Xi surgical system is performed. The dorsal vein complex (DVC) is sutured at the beginning of the procedure with two rounds of resorbable monofilament suture. To accelerate the return of continence, a modified Rocco stitch is performed in all patients. The anastomosis is performed by two tied V-loc stitches. No additional manipulation, such as fibrin glue or reinforcement with meshes, is allowed. Patients with rectal or bowel injury during the procedure will be excluded from evaluation.

For 3 h after the procedure, patients of both groups will stay in the intermediate care unit; after moving to the standard ward, blood samples will be obtained. On POD 1, all the patients will start with mobilization and solid food intake. The volume of the fluids in the drain will be measured on postoperative day 1, and if the volume will not exceed 200 ml for 24 h, the drain will be extracted. If the volume is higher than 200 ml/24 h and the creatinine level in drain fluid exceeds 500 μmol/l, urinary leakage will be confirmed [31]. On POD 2, the patients will be released for home care with an indwelling permanent urinary catheter. On POD 7, the urinary catheter and skin sutures will be extracted, and the blood sampling and ultrasound of the lower abdomen will be performed. Three months after the procedure, a follow-up visit is scheduled. The evidence of complication and level of prostatic specific antigen (PSA) is monitored.

Upon completion in 200 patients, the statistical processing will be performed, and patients will be unblinded.

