### Study population and eligibility criteria

All patients who are scheduled for operation due to low or intermediate risk prostate cancer in our institution will be screened and assessed for eligibility.

Only patients who will undergo robotic-assisted radical prostatectomy with suturing of dorsal complex vein (DVC) bundle at the beginning of the procedure without pelvic lymph node dissection will be included in the study. Patients with non-standard procedures or a procedure associated with higher morbidity will be excluded from the study to achieve a homogeneous study group.

Detailed inclusion and exclusion criteria are described below.

The following are the inclusion criteria:Patient scheduled for robotic-assisted radical prostatectomy without pelvic lymph node dissectionSigned informed consent providedBody mass index ≤ 35Age of patient ≤ 75 yearsOperating surgeon with experience of more than 100 cases

The following are the exclusion criteria:Body mass index > 35Age of the patient > 75 yearsCoagulation disorder (congenital or iatrogenic due to the chronic use of anticoagulants)Thromboembolic, cerebral, or an acute coronary event within the 6 months prior to prostatectomyChronic renal insufficiency (arbitrary cutoff level of creatinine 200 μmol/l)Allergic reaction to tranexamic acidOperating surgeon with experience < 100 casesPatient participating in another study

If subjects do not meet the inclusion criteria or withdraw their consent, they will be excluded from the study. The researcher will record the reason for their withdrawal.

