#### Criteria for discontinuing

A trial participant should terminate intervention if they wish to do so or if the investigator judges it necessary due to any of the following reasons:Withdrawal of informed consentPatient refusal or non-compliance to the protocolOccurrence of an unexpected serious adverse effectNon-standard procedure (non-sutured dorsal vein complex in the beginning of the procedure, rectal, small bowel, or ureteral wall injury)Other hemostyptic drug or material used during or after the procedure

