## Statistical methods

Each patient’s allocation to the analyzed population will be defined prior to the analysis and will be documented. In the full analysis set, patients will be analyzed as randomized according to the intention-to-treat principle. The intention-to-treat principle implies that the analysis includes all randomized patients. The per-protocol analysis set will include all the patients without major protocol deviation. Deviations from the protocol will be assessed as major or minor. Patients with major deviations from the protocol will be excluded from the protocol analysis. The safety analysis set will analyze the patients according to the treatment. The null hypothesis assumes that there is no difference in the hemoglobin level drop after the procedure in both groups. We will use a two-sample *T* tests allowing unequal variance with respect to the endpoint, which is the drop of hemoglobin levels. Differences between age and PSA will be assessed by the non-parametric Mann-Whitney *U* test. BMI and specimen weight will be compared by the Kolmogorov-Smirnov test. A *P*-value < 0.05 will be considered statistically significant. Statistical analyses will be performed using the NCSS statistical software (NCSS, Kaysville, UT, USA).

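### Exclusions for events after randomisation contradict the stated intention-to-treat analysis, and no analysis set is named as primary

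*Protocol article*

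**What the plan says.** **Analysis sets.** Statistical methods defines a full analysis set analysed as randomised and adds that "The intention-to-treat principle implies that the analysis includes all randomized patients". It also defines a per-protocol set of patients without major deviation, without listing the major deviations, and a safety set by treatment. It does not say which set is primary for the haemoglobin drop.

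**Exclusions elsewhere.**
- Study treatment: "Patients with rectal or bowel injury during the procedure will be excluded from evaluation".
- Data collection: "Patients with confirmed urinary leakage or urinoma will be excluded from the evaluation".
- Study population and eligibility criteria: "Patients with non-standard procedures or a procedure associated with higher morbidity will be excluded from the study to achieve a homogeneous study group". Criteria for discontinuing gives the content of a non-standard procedure: dorsal vein complex (DVC) not sutured at the start, or injury to the rectum, small bowel or ureter.
- Concealment mechanism foresees such removals: "If patients are excluded from the study after randomization, their numbers will not be reused".

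**Added haemostatic.** Criteria for discontinuing lists "Other hemostyptic drug or material used during or after the procedure". The sentence that introduces the list is "A trial participant should terminate intervention if they wish to do so or if the investigator judges it necessary".

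**The concern.** All randomised patients cannot be analysed if some are left out of the evaluation for what happened during or after the operation. Two analysts following this text could use different populations for the primary comparison, and both could cite the protocol.

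Two of the rules carry a particular risk:
- **Urinary leakage.** It is among the complications to be compared under Primary and secondary endpoints and is defined in Table 1. Excluding patients because they had it removes outcome events from the comparison.
- **Added haemostatic.** A surgeon plausibly adds one because the patient is bleeding, which is what the primary endpoint measures. If those patients are dropped and the drug works, more heavy bleeders leave the placebo arm than the treated arm, and the estimated difference shrinks. Blinding does not prevent this, because the selection acts through a consequence of treatment and not through knowledge of it.

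**Working it through.** **1. Timing.** "Participants will be randomly allocated to one of the groups before the surgical procedure after meeting the eligibility criteria" (Sequence generation). The single infusion is given within 5 min of docking (Implementation). Bowel or ureteral injury, an unsutured DVC, leakage and added haemostatic are all observed after randomisation.

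**2. The rules side by side.**

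| Event | Stated consequence | Limited to per-protocol set? |
|---|---|---|
| Rectal or bowel injury | Out of the evaluation (Study treatment) | No |
| Urinary leakage or urinoma | Out of the evaluation (Data collection) | No |
| Non-standard procedure | Out of the study (eligibility section, content from Criteria for discontinuing) | No |
| Added haemostatic | End the intervention, at the investigator's judgement | Not addressed |

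The first three rows conflict with the full analysis set as written. The fourth conflicts only by inference: after one completed infusion no intervention is left to end, so removal is the probable meaning, but it is not stated.

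**3. An SD for illustration.** The plan's 64 per group cannot be reproduced, because no SD is given. Solving backwards with α = 0.01 (two-sided assumed) and 90% power:

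SD = δ·√(n/2)/(z₀.₉₉₅ + z₀.₉₀) = δ × 5.657/(2.576 + 1.282) = 1.467δ.

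The protocol offers three values of δ: 5 (Sample size calculation), 8 (pilot) and 10 g/l (Primary and secondary endpoints). They give SD 7.3, 11.7 and 14.7. The noncentral t gives 7.2, 11.6 and 14.5, which are used in steps 4 and 5.

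**4. Hard cut.** Pilot POD 1 means are 25.6 (control) and 17.6 g/l (treated), a difference of 8.0. Assume normal drops and that every patient with a drop above T is removed. The mean of those kept is m − SD·φ(b)/Φ(b), with b = (T − m)/SD.

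For T = 45 and SD 14.5:
- Control: b = 1.338, mean = 25.6 − 14.5 × 0.1630/0.9095 = 23.0, with 9.0% removed.
- Treated: b = 1.890, mean = 17.6 − 14.5 × 0.0669/0.9706 = 16.6, with 2.9% removed.
- Difference 6.4 g/l, a loss of 1.6/8.0 = 20%.

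Remaining difference (g/l):

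| SD | T = 40 | T = 45 | T = 50 |
|---|---|---|---|
| 7.2 | 7.6 | 7.9 | 8.0 |
| 11.6 | 6.3 | 7.1 | 7.6 |
| 14.5 | 5.7 | 6.4 | 7.0 |

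**5. Noisy selection.** A haemostatic used during the operation is chosen before POD 1 haemoglobin is known, so a sharp cut is too strict. Let the log-odds of removal rise by 1 to 2 per SD of drop, with 6% removed overall, which matches the average in the worked case: (9.0 + 2.9)/2 = 6.0%. With SD 14.5 the remaining difference is 7.6 (slope 1) or 7.1 g/l (slope 2), a loss of 5 to 11%. SD 11.6 gives the same range.

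**6. Null cases.** If the true difference is zero, or removal is unrelated to bleeding, the bias in these models is zero.

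**7. Power if nobody is excluded.** Analysing 100 instead of 64 per group, at the implied SD and α = 0.01 two-sided, raises power at the design difference from 90% to 98.8%. This is an upper limit, since it assumes no missing POD 1 value.

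**The case against.** **The exclusions may be meant only for the per-protocol set.** That is a sensible reading and would remove the conflict. But no sentence says so, and two of the rules speak of evaluation without qualification. A separate analysis plan could settle it only by overriding one of the statements made here.

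**A reader might infer that the protocol orders patients with added haemostatic out of the analysis.** It does not. The item appears only under discretionary grounds for ending the intervention, and ending treatment differs from leaving the full analysis set. This part of the point is conditional, and so is the bleeding-related bias that depends on it. Bowel injury, the explicit case, is not shown to be frequent or related to treatment.

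**A reader might take 20% as the expected attenuation.** It comes from a sharp threshold and the largest of the three implied SDs. It is an upper-end illustration, and the noisy model with the same share removed loses 5 to 11%.

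**A reader might see the planned loss of over 33% as proof that these exclusions are intended.** Sample size calculation does not attribute the loss to them, and Data monitoring expects negligible dropout. That is a separate inconsistency.

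**A reader might conclude that complications will be hidden from the safety comparison.** This is not established in general: there is a separate safety set, and adverse events are to be recorded and followed without exempting these patients. What stands is narrower. The leakage rule, as worded, takes patients out of an evaluation in which leakage is an outcome.

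**The bias does not favour the drug.** In the models shown it runs towards no difference, so they show no risk of a false claim of efficacy.

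**Conclusion.** The contradiction holds on the text alone. It is explicit for rectal or bowel injury and for urinary leakage or urinoma, and it holds for non-standard procedures when the eligibility section is read with Criteria for discontinuing. Because the primary set is not named, the population for the primary comparison is not fixed. Confidence in this part is high and needs no figures.

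The bias from dropping patients with added haemostatic is conditional on that being the intended meaning. If it is, a true 8 g/l would be attenuated to about 7.1 to 7.6 g/l with noisy selection of 6%, and to between 5.7 and 8.0 g/l under hard cuts at 40 to 50 g/l with SD 7.2 to 14.5. These figures rest on the pilot means, normality, an SD implied by the sample size, and assumed removal rules. The documents give neither an SD nor exclusion rates.

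**What to change.** Before unblinding, in the protocol or the analysis plan:

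1. Name the full analysis set (all randomised patients, in the group allocated) as primary for the POD 1 haemoglobin drop.
2. Delete the exclusion from evaluation in Study treatment and in Data collection.
3. Classify the events in those two sections, the eligibility section and Criteria for discontinuing as deviations or events that affect only the per-protocol sensitivity analysis.
4. State that meeting a discontinuation criterion does not remove a patient from the full or safety analysis sets. The clinical criteria themselves need not change for this.
5. Use the POD 1 haemoglobin and complication data already scheduled for these patients, and count urinary leakage as an outcome.
6. Report added haemostatic use by arm.

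The cost is a wording change. The scheduled blood samples and the 3-month visit already supply the data. Atypical operations may add slightly to the outcome variance, and the larger number analysed should more than offset that.
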